### Who will take informed consent? {26a}

Voluntary participation and written informed consent by therapists, patients, and their caregivers are necessary conditions for participation in the study. Therapists who want to participate in MARS-CA sign the informed consent before participating in the two study preparation workshops. On patients’ side, the study is typically introduced by a MARS-CA therapist at the first therapy session to the juvenile patient and the caregivers. If the patient shows interest in the participation of the study, both the patient and the caregivers are asked to sign the informed consent. The local ethics committee of the Faculty of Behavioral and Cultural Studies at the University of Heidelberg approved the study protocol in accordance with the Helsinki Declaration.

### Additional consent provisions for collection and use of participant data and biological specimens {26b}

Not applicable, no additional consent provisions for collection and use of participant data and biological specimens in ancillary studies.

### Interventions

#### Explanation for the choice of comparators {6b}

Participants in the control groups will start their therapy sessions either with a relaxation intervention (SIRI, active control condition) or with no session-introducing intervention (non-active control condition). The relaxation exercises have been chosen as comparators as they are a well-established CBT intervention method to reduce inner tension and agitation. No session-introducing intervention has been chosen as comparator because such a non-active comparator will reveal general differences to the active intervention methods.

#### Intervention description {11a}

Depending on the condition (IG-M vs. CG-R vs. CG), three different SIMI, three different SIRI, or no session-introducing intervention will be conducted. With regard to the SIMI, [name] (JK) and [name] (JM) have composed versions for MARS-CA based on the following interventions: mindful walking, body scan, and breathing space of the MBCT-C program by Semple and Lee [18]. During the mindful walking intervention, patients are asked to pace up and down the therapy room and to perceive their movements with an accepting attitude [18]. In the body scan intervention, patients are expected to perceive one part of the body after another in the here and now with reducing the appraisal of thoughts, emotions, and physical sensations to a minimum. The breathing space intervention is some kind of “mini-meditation” during which the patients firstly become aware of their thoughts, emotions, and physical sensations in the present moment, secondly put their focus solely on their breathing, and thirdly extend their awareness beyond their breathing again [18]. The SIRI comprise a self-developed walking relaxation intervention, an adapted version of the progressive muscle relaxation (PMR) for children [36], and an adapted version of the Captain Nemo imagery journey “dolphin riding” [37]. The self-developed walking relaxation intervention has been designed by the authors, together with a child and adolescent psychotherapist having long-term experience in relaxation exercises. It starts with the patients clapping their hands until they have found an appropriate rhythm. In the next step, patients are asked to further clap their hands and to additionally walk through the therapy room, suitable to the clap rhythm. During the PMR intervention, patients are invited to briefly tense and relax single muscle groups in alternation. The intervention ends in tensing and relaxing of all muscle groups of the body [36]. The imagery journey intervention, an adapted version of the Captain Nemo imagery journey “dolphin riding,” consists of an underwater excursion during which the patients imaginatively meet some friendly dolphins [37].

All interventions have been assessed for eligibility by a sample of juvenile patients with mental disorders. In the IG-M and the CG-R, each intervention will be instructed by the trainee therapist at the beginning of the first 24 therapy sessions eight times in total, more precisely four times during the first twelve therapy sessions and four times during the second twelve therapy sessions. The interventions of the IG-M and CG-R are parallelized to each other (mindful walking—walking relaxation (length of both interventions: 4 min 15 s); body scan—PMR (length of both interventions: 4 min 40 s); breathing space—imagery journey (length of both interventions: 7 min 30 s)). An overview of the study procedure is depicted in Fig. 2.

**Fig. 2 Fig2:**
[figure not shown]
Study procedure of MARS-CA. IG-M, intervention group mindfulness; CG-R, control group relaxation; CG, control group; PMR, progressive muscle relaxation; S, therapy session

#### Criteria for discontinuing or modifying allocated interventions {11b}

Not applicable, no discontinuing or modifying allocated interventions envisaged.

#### Strategies to improve adherence to interventions {11c}

Potential adherence effects are assessed by a self-designed adherence scale.

#### Relevant concomitant care permitted or prohibited during the trial {11d}

Any potential concomitant care will be assessed via questionnaires and will be statistically controlled.

#### Provisions for post-trial care {30}

Not applicable, no provisions for ancillary and post-trial care or compensation to those who suffer harm from trial participation.

#### Outcomes {12}

In the following, the assessment of diagnoses, primary and secondary outcome measures as well as the assessment of demographics, adherence, and therapeutic techniques will be described. For a tabular overview of all measurements, see Table 1.

**Table 1 Tab1:** Participant timeline of the Mindfulness and Relaxation Study – Children and Adolescents (MARS-CA)

Measures	Before outpatient admission	Diagnostic phase	Pre	S_**1–**_S_**24**_	Mid-S_**3**_	Mid-S_**10**_	Mid-S_**17**_	Post-S_**24**_	6-month follow-up
**Recruitment—therapist**									
Informed consent	+								
**Clinical assessment—therapist**									
HICBI					+	+	+	+	
CEQ therapist					+	+	+	+	
AD-S therapist					+	+	+	+	
**Recruitment—patient**									
Informed consent patient		+							
Informed consent caregiver (patient age < 18 years)		+							
Eligibility screen		+							
Allocation		+							
**Clinical assessment—patient**									
Kinder-DIPS-OA (including severity measurement)			+					+	
YSR 11-18R			+		+	+	+	+	+
DISYPS-III									
SBB-DES			+		+	+	+	+	+
SBB-ANG			+		+	+	+	+	+
SBB-ADHS			+		+	+	+	+	+
CEQ patient					+	+	+	+	
AD-S patient					+	+	+	+	

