### Objectives {7}

The main purpose of the study is to investigate whether session-introducing mindfulness interventions (SIMI) in comparison to session-introducing relaxation interventions (SIRI) and no specific intervention at the beginning of individual psychotherapy sessions with children and adolescents between 11 and 19 years of age have a positive impact on the therapeutic process. Session-introducing intervention means that in the first 5 to 10 min of a 50-min therapy session, either a short mindfulness intervention, or a short relaxation intervention, or no specific intervention (but the proceeding as usual) will be conducted. This session-introducing intervention could foster self-acceptance and help to focus attention on the present moment of the session, therefore strengthening the therapeutic alliance and outcome effects. Specifically, we want to investigate if SIMI in comparison to SIRI and no intervention at the beginning of psychotherapy sessions lead to a reduction in psychopathological symptomatology and to an improvement of the therapeutic alliance. Furthermore, we hypothesize that the mindfulness condition moderates the relationship between therapeutic alliance and symptomatic outcome. Before the start of therapeutic treatment, patients will be randomized either to the intervention group, practicing SIMI at the beginning of the therapy sessions (IG-M), or to the active control group, practicing SIRI at the beginning of the therapy sessions (CG-R), or to the control group with no specific interventions at the beginning of the therapy sessions (CG). We will investigate the following hypotheses:

H1) We hypothesize that patients of the IG-M will improve more in symptomatic outcome in comparison to the CG-R and CG.

H2) We hypothesize that both patients and therapists of the IG-M will experience stronger increases of therapeutic alliance across the course of therapy in comparison to the CG-R and CG.

H3) We hypothesize that the mindfulness condition moderates the relationship between therapeutic alliance and symptomatic outcome.

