#### Diagnoses

Diagnostic Interview for Mental Disorders in Children and Adolescents - Open Access including severity measurements for the main diagnoses [38], according to the ICD-10 [39] and DSM-5 criteria [40], will be applied to establish the diagnoses in patients under the age of 18 years. For patients aged 18 years or older, the Structured Clinical Interview (SCID; [41]) will be applied. All diagnostic interviews will be recorded on video.

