### Assignment of interventions: allocation

#### Sequence generation {16a}

Participants in the study will start their therapy sessions either with a SIMI, a SIRI, or no intervention. Treatment allocation will be performed by a blocked and stratified randomization process with a computerized random number generator. Patients will be stratified according to their main diagnosis (hyperkinetic disorder, depression, or anxiety disorder) and then equally randomized into one of the three treatment arms by a balanced blocking procedure.

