### Assignment of interventions: blinding

#### Who will be blinded {17a}

The focus of the current study is on external validity and generalizability of the results to routine clinical practice. Consequently, according to extension of the CONSORT statement concerning the criteria of a pragmatic randomized controlled trial [47, 48], in the current study, no blinding will be implemented.

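### As printed, Table 1 places eligibility and open allocation before the diagnostic interview and the baseline YSR, and the consent section fits neither; one sequence must be fixed.

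*Protocol article*

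**What the plan says.** Participant timeline {13} refers the reader to Table 1. The first three columns of that table are Before outpatient admission, "Diagnostic phase" and Pre. In the block Recruitment—patient, the rows for consent, "Eligibility screen" and allocation are marked only in the second column. In the block Clinical assessment—patient, the row "Kinder-DIPS-OA (including severity measurement") is marked at Pre and at Post-S24, and the YSR from Pre onwards. Neither is marked in the diagnostic phase.

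The text adds the following:

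- Diagnoses: the interview "will be applied to establish the diagnoses in patients under the age of 18 years"; a different interview serves those aged 18 or over.
- Eligibility criteria {10}: inclusion requires a primary hyperkinetic, depressive or anxiety disorder.
- Sequence generation {16a}: "Patients will be stratified according to their main diagnosis (hyperkinetic disorder, depression, or anxiety disorder) and then equally randomized".
- Objectives {7}: "Before the start of therapeutic treatment, patients will be randomized either to the intervention group".
- Primary outcome measures: the first YSR is taken before therapy starts.
- Who will take informed consent? {26a}: "the study is typically introduced by a MARS-CA therapist at the first therapy session to the juvenile patient and the caregivers". Patient and caregivers are then asked to sign.
- Who will be blinded {17a}: "in the current study, no blinding will be implemented".

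**The concern.** Two separate things are at stake.

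The first is the baseline. The primary outcome is the patient's own report, and the primary hypothesis is tested as a group-by-time interaction with pre as the first time point (Sample size {14}; Statistical methods {20a}). If a patient fills in the pre YSR already knowing the arm, disappointment or expectation can shift the score differently between arms. A difference of that kind at the first time point enters the interaction directly, and the later data cannot separate it from a treatment effect. The other Pre measures (the DISYPS-III scales and the mindfulness, self-compassion and empathy questionnaires) share the exposure.

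The second is the diagnosis. If eligibility and stratum are settled before the interview that establishes the diagnosis, some patients may be randomised in the wrong stratum or may turn out not to meet the inclusion criterion. The article gives no rule for a patient whose interview contradicts what was already fixed.

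**Working it through.** **Order of events, place by place**

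| Step | Table 1 | Text |
|---|---|---|
| Consent | Diagnostic phase | typically first therapy session ({26a}) |
| Eligibility | Diagnostic phase | needs the primary diagnosis ({10}) |
| Allocation | Diagnostic phase | before treatment ({7}); stratified by main diagnosis ({16a}) |
| Diagnostic interview | Pre | establishes the diagnosis (Diagnoses) |
| First YSR | Pre | before therapy (Primary outcome measures) |
| Disclosure of the arm | not shown | not stated |

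The header and the rows of Table 1 have the same number of cells, so the marks do line up with these columns.

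Three conflicts follow:

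1. Eligibility and stratum need the diagnosis, but Table 1 completes both one column before the interview.
2. Objectives and Primary outcome measures place randomisation and the pre YSR before therapy without ordering the two. Table 1 is the only place that orders them, and it puts allocation first.
3. Consent at the first therapy session cannot precede a randomisation and a pre YSR that both come before therapy. Session 1 already belongs to the 24 sessions with an introducing intervention (Intervention description {11a}) and carries an alliance rating (Table 1, S1–S24).

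**Scale of the baseline risk (illustration)**

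Inputs from Sample size {14}: f = 0.12, k = 3 groups, m = 5 measurements, correlation 0.5, nonsphericity correction 1, α = 0.05, power 0.80.

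The plan's own figure comes first. With λ = f²·N·m/(1 − r), df1 = (k − 1)(m − 1) = 8 and df2 = (N − k)(m − 1), N = 108 gives λ = 0.0144 × 108 × 5/0.5 = 15.55, df2 = 420 and power 0.808. The smallest sufficient N is 107, or 108 in equal groups. The stated 108 reproduces.

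Now assume no true effect and a shift of δ SD in the pre score of the mindfulness arm alone. One displaced cell in a 3 × 5 layout gives f = √[δ² × (2/3) × (4/5)/15]. The δ values are assumptions; the protocol gives none.

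| δ (SD) | f | Rejection rate, N = 108 | Rejection rate, N = 135 |
|---|---|---|---|
| 0.1 | 0.019 | 6% | 7% |
| 0.2 | 0.038 | 11% | 13% |
| 0.3 | 0.057 | 20% | 25% |
| 0.5 | 0.094 | 56% | 68% |

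To match the planned f = 0.12 by itself, the shift would have to be 0.12/√[(2/3)(4/5)/15] = 0.64 SD. The required sample size does not depend on the sequence.

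**The case against.** The case against rests on how far Table 1 can be pressed. Its columns are not strictly chronological: S1–S24 stands before Mid-S3 and spans all the mid and post occasions. Pre may be only a measurement label paired with Post, since the interview is marked at exactly those two points. Read literally, the diagnostic phase would contain no diagnostic instrument, which is implausible. Sequence generation implies that a diagnosis is in hand before randomisation. The flow chart and the procedure figure are not shown and might give the order. An independent assistant holds the list and makes the assignment ({16b}, {16c}), so assignment and disclosure need not coincide. First therapy session may also be loose wording for a first contact.

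Much of this stands. The columns may overlap, and a working diagnosis may exist when patients are allocated. A reader might infer that the baseline is in fact distorted; the document does not support that, because nowhere does it say when patient or therapist learns the arm. A reader might also infer that patients will be excluded after allocation by staff who know the arm. That has little support: a revised diagnosis is not among the drop-out criteria, and an intention-to-treat analysis is planned ({20c}). A shift of 0.1 SD would also barely move the planned test.

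What remains is that Table 1 disagrees with the text on diagnosis, and no sentence places the pre YSR before disclosure. The consent section also conflicts with the rest, even if the columns overlap. If the figures show a different order, Table 1 and the consent section still need correcting.

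**Conclusion.** The point holds as an inconsistency in the stated sequence that leaves an avoidable route to bias. Followed as printed, the timeline puts an open allocation before a self-reported primary baseline and before the interview that defines eligibility and stratum. The baseline is open to bias, and the stratum may rest on an unconfirmed diagnosis.

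The size cannot be taken from the document. Under the assumed one-arm shifts the effect on the 5% test is slight at 0.1 SD (about 6%) and material at 0.2 to 0.3 SD (about 11% to 20% at N = 108). Its direction is unknown. The illustration uses the repeated-measures ANOVA that the protocol itself takes as a proxy for its multilevel model, and it assumes that the shift affects only the pre score of one arm.

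**What to change.** State one sequence, and make Table 1, Who will take informed consent? {26a}, Diagnoses and Sequence generation {16a} agree with it: consent; diagnostic interview (including the one used from age 18); eligibility; pre YSR and all other pre questionnaires completed; release of the allocation by the independent assistant; session 1. Say explicitly that neither patient nor therapist learns the arm before the pre questionnaires are complete.

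For patients already enrolled, compare the date of the pre YSR with the date on which the arm was disclosed. If the order was mixed, report a sensitivity analysis restricted to patients whose baseline came first. If every baseline came before disclosure, say so. If every baseline came after it, no such analysis is possible and the limitation should be reported.

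The cost is a short wait before the therapist learns the arm. No assessment is added, and the independent assistant is already in place. Trial status expects recruitment until about July 2023, so patients enrolled after the correction benefit; a baseline taken after disclosure cannot be recovered later.

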**Mindfulness and mindfulness-related assessment—therapists**									
KIMS-D			+		+	+	+	+	+
SCS-D			+		+	+	+	+	+
ESSW			+		+	+	+	+	+
TPI therapist					+	+	+	+	
**Mindfulness and mindfulness-related assessment—patients**									
CAMM			+		+	+	+	+	+
SCS (child version)			+		+	+	+	+	+
TPI patient					+	+	+	+	
PQ-M					+	+	+	+	
**Post-session questionnaire—therapists**									
FTB-KJ therapist				+					
TPI (short version) therapist				+					
**Post-session questionnaire—patients**									
FTB-KJ patient				+					
TPI (short version) patient				+					

*Abbreviations*: *AD-S* Adherence Scale, *CAMM* Child and Adolescent Mindfulness Measure, *CEQ* Credibility-/Expectancy Questionnaire, *DISYPS-III* Diagnostic System for Mental Disorders in Childhood and Adolescence, 3rd version, *FTB-KJ* German version of the Therapeutic Alliance Scale for Children, *ESSW* Empathy Scale for Social Workers, *HICBI* Heidelberg Inventory of Cognitive-Behavioral Interventions, *KIMS-D* German version of the Kentucky Inventory of Mindfulness Skills, *PQ-M* Practice Quality – Mindfulness, S therapy session, *SBB-ADHS* problem scales of the attention-deficit/hyperactivity disorder self-rating scale, *SBB-ANG* problem scales of the anxiety disorder self-rating scale, *SBB-DES* problem scales of the depressive disorder self-rating scale, *SCS-D* German version of the Self-Compassion Scale, *TPI* Therapeutic Presence Inventory, *YSR 11-18R* Youth Self Report Revision

#### Diagnoses

Diagnostic Interview for Mental Disorders in Children and Adolescents - Open Access including severity measurements for the main diagnoses [38], according to the ICD-10 [39] and DSM-5 criteria [40], will be applied to establish the diagnoses in patients under the age of 18 years. For patients aged 18 years or older, the Structured Clinical Interview (SCID; [41]) will be applied. All diagnostic interviews will be recorded on video.

#### Primary outcome measures

The primary outcome of the study is patients’ general psychopathological symptomatology (assessed by the total score of the Youth Self-Report 11-18R (YSR 11-18R; [42]). The total score of the YSR-11-18R comprises items related to symptoms of anxiety, depression, somatic complaints, social problems, thought problems, attention problems, rule-breaking behavior, and aggressive behavior [42]. The YSR 11-18R will be assessed before the start of therapy (pre), at the 3rd therapy session (mid-S_3_), at the 10th therapy session (mid-S_10_), at the 17th therapy session (mid-S_17_), at the 24th therapy session (post), and at 6-month follow-up (for more details, see Table 1). Of primary interest are change trajectories of the general psychopathology over the course of therapy. We will assess and compare change trajectories of the three treatment conditions using multilevel-models.

#### Secondary outcome measures

The secondary outcome measures comprise therapeutic alliance, development of mindfulness, self-compassion, and empathy as well as depressive, anxiety, and hyperkinetic symptoms. All questionnaires concerning the secondary outcome measures will be assessed before the start of therapy (pre), at the 3rd therapy session (mid-S_3_), at the 10th therapy session (mid-S_10_), at the 17th therapy session (mid-S_17_), at the 24th therapy session (post), and at 6-month follow-up (for more details, see Table 1).

#### Participant timeline {13}

The participant timeline is depicted in Table 1.

#### Sample size {14}

A recent meta-analysis has detected small to medium effects of MBIs in RCTs with youth in depression (*d* = 0.27), anxiety (*d* = 0.16), executive functions (*d* = 0.30), and attention (*d* = 0.19) [24]. A meta-analysis that has analyzed the effects of meditation in non-clinical groups of adult meditators has detected moderate effect sizes for meditation compared to relaxation (*r* = .21) on psychological outcomes [43].

Taking these results into account, power analyses with G*Power [44] for the detection of small to medium-sized effects (Cohen’s *f* = 0.12) for the interaction between time (pre, T3, T10, T17, T24) and treatment condition (IG-M vs. CG-R vs. CG) (analysis of variance (ANOVA) repeated measures, within-between-interaction, *α* = 0.05, power (1 − β) = 0.80, number of groups = 3, number of measurements = 5, pre–post correlation *r* = 0.5, nonsphericity correction = 1) for the YSR 11-18R total score primary outcome resulted in a sample size of 108 patients. Although this should only be seen as a proxy for the power of the reported multilevel models (MLMs), previous research showed that power in MLM is often comparable to (or even higher than) power in an ANOVA design [45, 46]. The planned sample size should, therefore, be considered a conservative estimate required to detect a small to medium sized condition × time interaction. Taking a drop-out-rate of about 25% into account (i.e., 27 patients), a total sample of 135 patients will be assigned to one of the three treatment groups by a stratified randomization process.

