Meta-analyses including both non-clinical and clinical samples revealed small-to-moderate effect sizes (Becker’s del, a measure for the difference of pre-post effect sizes = 0.2–0.5; *g* = 0.305–0.462) of MBIs on treatment effects [4, 23]. A meta-analysis focused on both clinical and non-clinical randomized trials [24], revealing small positive effects of MBIs on mindfulness, executive functioning, attention, depression, anxiety/stress, and negative behavior (*d* ranging 0.16–0.30; [24]). Taking only RCTs with active control treatments into account reduced the number of significant areas with positive effect sizes to mindfulness (*d* = 0.42), depression (*d* = 0.47), and anxiety/stress (*d* = 0.18) [24]. However, the effect sizes in these areas increased from small effect sizes to moderate effect sizes (with the exception of anxiety/stress), indicating that MBIs are more effective than other treatments [24]. It should be noted that the studies with an active control condition included in this meta-analysis have not been conducted in a clinical setting.

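### The planning effect f = 0.12 is not equivalent to the cited d = 0.16–0.30: in the 3 × 5 interaction it means a difference in change of about 0.7 SD under linear divergence

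*Protocol article*

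**What the plan says.** Protocol article, Sample size {14}, opens with a meta-analysis reporting "small to medium effects of MBIs in RCTs with youth in depression" (0.27), anxiety (0.16), executive functions (0.30) and attention (0.19). It adds an adult meta-analysis of meditation against relaxation with r = .21. On the strength of these it reports a G*Power calculation "for the detection of small to medium-sized effects (Cohen’s *f* = 0.12) for the interaction between time (pre, T3, T10, T17, T24) and treatment condition". The procedure is ANOVA, "repeated measures, within-between-interaction", with alpha 0.05, power 0.80, "number of groups = 3, number of measurements = 5", correlation 0.5 and nonsphericity correction 1. The result is 108 patients, raised to 135 for dropout.

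The section then notes that multilevel models often have power comparable to or above that of ANOVA, and concludes that the planned size "should, therefore, be considered a conservative estimate required to detect a small to medium sized condition" × time interaction. It shows no conversion from d or r to f, and does not express f = 0.12 as a difference in change, in SD units or in Youth Self-Report (YSR) points.

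The section on mindfulness programs in child and adolescent psychotherapy describes the same youth meta-analysis as "revealing small positive effects of MBIs on mindfulness, executive functioning, attention, depression, anxiety/stress, and negative behavior" (d from 0.16 to 0.30). It also gives larger values for trials with active controls: 0.42 for mindfulness, 0.47 for depression and 0.18 for anxiety/stress, none of them from a clinical setting.

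**The concern.** The sample size section puts the same label, small to medium, on the cited youth d values and on f = 0.12, and presents the first as the reason for the second. A reader will conclude that a trial of this size has about 80% power for effects such as d = 0.16 to 0.30 on the YSR total score. A standardised difference between two groups and Cohen's f for a 3 × 5 interaction are different quantities. If the same f requires a much larger d, the implied power is not there, and a null result on the primary outcome could be misread as evidence against effects of the cited size.

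**Working it through.** **Inputs.** From Sample size {14}: f = 0.12, k = 3 arms, m = 5 occasions, ρ = 0.5, ε = 1, α = 0.05, N = 108. Equal allocation is from Sequence generation {16a}. The direction of effect (IG-M better than both controls) is hypothesis H1. The shape of the effect over time is not stated, so the shapes below are assumptions.

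**1. The plan's own figure.** λ = f²·N·m/(1−ρ) = 0.0144 × 108 × 5/0.5 = 15.55, with df₁ = (3−1)(5−1) = 8 and df₂ = (108−3)(5−1) = 420. Power is 0.808. At N = 105 it is 0.794, so 108 is the smallest multiple of 3 that reaches 0.80. This also fixes what f means here: the SD of the 15 interaction effects divided by the within-cell outcome SD.

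**2. From f to a difference in change, d.** If both controls share one time course, f² = (variance of the arm pattern 1, 0, 0) × (variance of the time pattern) × d². The arm variance is 2/9. For a linear course over sessions 0, 3, 10, 17, 24 (divided by 24) the time variance is 0.1357, so f = √(0.2222 × 0.1357)·d = 0.174d.

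| Shape of IG-M's lead | f | d at f = 0.12 |
|---|---|---|
| Linear in session number, equal controls | 0.174d | 0.69 |
| Linear, equally spaced occasions, equal controls | 0.167d | 0.72 |
| Linear, equally spaced occasions, CG-R midway between IG-M and CG | 0.144d | 0.83 |
| Full lead from S3, equal controls | 0.189d | 0.64 |
| Full lead from S10, equal controls (least d if controls share one course) | 0.231d | 0.52 |
| Lead over one control from S10 and over the other at S24 (least d if leads never shrink) | 0.267d | 0.45 |
| Lead over one control at S3 and S10 only, over the other at S17 and S24 only (extreme case) | 0.377d | 0.32 |

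The last three rows come from enumerating all patterns with no difference at baseline and a lead of 0 or d over each control at each later occasion.

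**3. Power at N = 108, linear in session number, equal controls.** The omnibus test uses f = 0.174d in step 1. The slope models use a random intercept with residual variance 1−ρ = 0.5. The variance of one arm's slope, scaled as pre-to-S24 change, is 0.5/(36 × 5 × 0.1357) = 0.0205. For IG-M against pooled controls, SE = √(1.5 × 0.0205) = 0.175. For the 2-df test, λ = (2/3)d²/0.0205.

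| d | Omnibus, 8 df | Slope, 2 df | IG-M vs pooled controls |
|---|---|---|---|
| 0.16 | 0.08 | 0.12 | 0.15 |
| 0.30 | 0.18 | 0.31 | 0.40 |
| 0.43 | 0.35 | 0.58 | 0.69 |
| 0.47 | 0.42 | 0.66 | 0.76 |
| d with 80% power | 0.69 | 0.55 | 0.49 |

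The value 0.43 is 2r/√(1−r²) at r = .21. The value 0.47 is the larger active-control youth effect. A simulation of the 3 × 5 ANOVA (equally spaced occasions, 36 per arm, 4,000 runs) gave power 0.82 at 0.72 SD, 0.16 at 0.30 SD and 0.08 at 0.16 SD, in line with the formula.

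**4. Most favourable shapes at d = 0.30, omnibus test, N = 108.** Power is 0.30 for the full lead from S10, 0.40 for the best pattern in which leads never shrink, and 0.75 for the extreme pattern. If all 135 patients were analysed without loss, the pooled slope contrast under linear divergence would reach 0.48. Only the extreme pattern would then pass 80% on the omnibus test: λ = (0.377 × 0.30)² × 135 × 5/0.5 = 17.3, power 0.86.

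**The case against.** - **The label.** f = 0.12 lies between Cohen's conventional small (0.10) and medium (0.25) values of f. A reader might infer that calling it small to medium is an error. As a description of f it is not. The difficulty is that the same words also cover the cited d values.
- **Conservative.** In context the word follows from the remark that multilevel models may have more power than ANOVA. Read that way it has support: at 0.69 SD the omnibus test has about 0.80 power and the 2-df slope model about 0.95. It does not support a claim of caution about effects of the cited size.
- **The conversion.** A reader might infer that f was obtained by halving a d of about 0.24, which is the two-group rule. The protocol article does not say so, and the point does not need it. Nor does the article state outright that it has 80% power for d = 0.16 to 0.30. That is the natural reading of the link it draws.
- **The shape.** The figure of 0.7 SD depends on linear divergence from two equal controls, and 0.52 SD might be taken as a floor for any shape. It is not, because the protocol does not assume that relaxation and no intervention behave alike over time. Differing controls lower the minimum to 0.45 SD, or to 0.32 SD if leads may vanish again.
- **Larger cited effects.** The article also gives youth effects of 0.42 and 0.47 against active controls, so 0.30 is the largest youth value only within the sample size section. At 0.47 the gap is much smaller, but linear-pattern power at N = 108 still does not reach 80% with any of the three tests.

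**Conclusion.** The concern holds as a mismatch between the cited evidence and the planning effect. There is no arithmetic error: someone might infer that N = 108 is wrong, but it follows from the stated inputs.

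Under linear divergence f = 0.12 means about 0.7 SD, more than twice the largest d cited in the sample size section. The size of that gap depends on the shape, but the conclusion for d = 0.16 to 0.30 does not: at N = 108 no pattern with leads between 0 and d gives the omnibus test 80% power. The more efficient slope models stay at or below about 0.40 at d = 0.30 under linear divergence.

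These figures assume ρ = 0.5, sphericity and, for the slope models, a random intercept only. They ignore the therapist level that Statistical methods {20a} plans to include.

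**What to change.** Keep the sample size and revise the paragraph in Sample size {14}:

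- State the detectable difference in pre-to-S24 change in SD units, with its assumptions: about 0.7 SD for the omnibus interaction, about 0.55 SD for a 2-df slope multilevel model and about 0.5 SD for IG-M against pooled controls. All are at N = 108 and ρ = 0.5, with IG-M diverging linearly from two equal controls.
- Report the power for the cited d = 0.16 to 0.30 under the same assumptions: 0.08 to 0.18, 0.12 to 0.31 and 0.15 to 0.40 respectively.
- Do not present the size as adequate or conservative for effects of that size. Keep the word conservative only as a comparison of ANOVA with the multilevel model at the same effect.
- Keep the label small to medium only where it is tied to Cohen's f, and do not equate it with the cited d values.

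The cost is the rewording of one paragraph and a less favourable stated detectable effect. No patients are added, and the design and analysis do not change.
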